### Randomisation of participants

Participating patients of GPs who had received the training were randomly allocated to intervention and control groups by the independent study centre using a computer generated allocation sequence. People living in the same household were allocated to the same group. The ratio of allocation of participants to intervention and control groups was 1:1 in the London sample and 1:2 in the Hamburg sample. In the Solothurn sample, a 1:1 randomisation ratio was used in the initial study phase, and then changed to 1:2, resulting in an average ratio of 1:1.6. Variation in randomisation rates was related to budgetary constraints (see sample size calculation), which became apparent after the project was underway. Participants allocated to the intervention group were offered HRA-O with personal reinforcement. Those allocated to the control group received usual care.

Participants of GPs who had not received additional training formed the concurrent comparison group. All patients in this group continued to receive usual care during the study period. GPs in this group received only general project information during the study period, and were offered the training after the end of the project follow-up.

Final inclusion of study participants started in November 2000 and was completed in London in October 2001, in Hamburg in September 2001, and in Solothurn in February 2002.

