#### Use of HRA-O instrument

The intervention is based on the HRA-O instrument consisting of a self-administered HRA-O questionnaire, a personalised feed-back report to the older person and a summary feed-back report for the GP or the health educator. The development, practicability and performance of the HRA-O questionnaire are described in a separate publication [7]. Briefly, the HRA-O questionnaire contains the following sections: Administrative information (name, address, date of birth, date of completion, completion time); self-reported chronic conditions, preventative care use, medication use, signs and symptoms, self-perceived health, physical activity, nutrition, injury prevention, tobacco use, alcohol use, eyesight, hearing, depressive symptoms, self-reported memory, social network, social support, basic and instrumental activities of daily living, socio-economic information (education, occupation, living arrangement, and selected additional items at each site, such as information on state pension in London), and health measurements (weight, height, blood pressure, cholesterol). In addition, it contains additional items based on the transtheoretical model of behaviour change, as a basis for addressing the participants' readiness to change and self-perceived barriers to changing health behaviour in the feed-back statements [13]. Completed questionnaires are entered into the computer, and an algorithm-based method automatically generates summary reports for the involved health professionals, as well as personalised feed-back reports for the participants. This includes individually tailored information and recommendations based on the older persons' responses to the questionnaire, general health information on each domain addressed in the HRA-O questionnaire, and sources of further information in the community.

In the PRO-AGE study, GPs or the study centre posted the approximately 34-page HRA-O questionnaire to all individuals allocated to the intervention arm and asked them to complete the questionnaire on their own or with the support of a proxy [7]. Participants who completed the HRA-O questionnaire and their health care providers received the computer-generated personalised feed-back reports generated by the study centre at each project site.

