#### Additional reinforcement in Hamburg

In Hamburg, all patients allocated to the intervention group were invited to participate in a 4-hour group session at a geriatric centre or to receive two home visits by a specially trained nurse [15-18]. Group sessions were given jointly by an interdisciplinary team consisting of a geriatrician, a physical therapist, a nutritionist, and a social worker working with a structured programme focusing first on successful aging, nutrition, preventative care, lifestyle modification, physical activity, medication use, social contacts, housing and living location and emphasising patient self-efficacy and empowerment. The second part of the group session covered nutrition and physical activity in more detail. The purpose was to encourage the setting of individual goals. In the third part of the group session participants received individual written recommendations from members of the interdisciplinary team [15,16]. Older persons who preferred home visits were offered two home visits (after base-line and at six months) by a specially trained nurse who conducted an additional multidimensional assessment of nutrition, medication use, pain, mobility, cognition, vision, and hearing, prioritised recommendations and follow-up for adherence with the recommendations [17,18].

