#### Additional reinforcement in Solothurn

In Solothurn, all participants who returned the HRA-O questionnaire were offered home visits by specially trained health nurses. The nurses discussed the participant feed-back on the completed HRA-O questionnaire with the older persons, answered questions from patients, and conducted a detailed interview on physical activity and medication use in all patients. If needed, they conducted additional assessments in the areas of nutrition, medication use, pain, mobility, cognition, vision, and hearing. Nurses discussed each case with a project geriatrician, and subsequently with the GP. Recommendations were prioritised, reinforced or formulated in more detail (e.g., definition of specific recommendations related to physical activity), and if new risks were identified, new recommendations were formulated. Based on the transtheoretical model of behaviour change nurses attempted to achieve behaviour change by taking into account individual readiness to change and negotiating realistic goals with the older persons. Subsequently, nurses conducted follow-up visits at 6-monthly intervals, with interim phone calls to patients as needed over a two-year period. At one year, the nurses conducted a yearly assessment home visit based on the follow-up HRA-O and on additional assessments as needed. Further funding, secured once the project was underway, enabled the duration of the intervention to be extended to two years in Solothurn. This allowed longer-term follow-up of the effects of HRA-O combined with preventive home visits.

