### Data collection

Prior to randomisation, participant age and gender were recorded from practice registers. Information on base-line self-perceived health status, prior health care use, and instrumental support were derived from the Pra questionnaire [10]. In addition, for the participants in London, the Townsend score [19], a measure of social deprivation based on indicators of the older person's living location, was derived from the participants' address information.

At the one-year follow-up, surviving participants of all groups (intervention, control, and concurrent comparison group) were sent a HRA-O questionnaire with additional questions on health care use [10] and on patient self-efficacy [20]. This follow-up questionnaire included all items required for outcome analysis, as listed in Table 2. In addition, the one-year follow-up questionnaire was used for obtaining information on socioeconomic information and self-reported chronic conditions among participants in the control and concurrent comparison groups. No reminders were sent to persons not returning this questionnaire. To reduce the amount of missing information on preventative care in the London sample, practices were asked to review patient medical records for information on preventative care use (vaccination coverage, blood glucose and cholesterol measurement, colon cancer screening) for patients who had returned the 1-year follow-up questionnaire but had incomplete information on some items of preventative care (n = 44 intervention group, n = 33 control group, n = 20 concurrent comparison group).

**Table 2 T2:** List of primary outcomes used in the PRO-AGE study at the follow-up: health behaviour and preventative care use

**Domain**	**One-year outcome analysis (all sites)**	**Two-year outcome analysis (Solothurn only)**

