Outcome analyses of the randomised controlled study will be conducted for each site separately in keeping with the inter-site variations of reinforcement methods. The main analyses will compare primary and secondary outcomes between intervention and control groups at follow-up. In these analyses, the fact that participants living in the same household were allocated to the same group will be taken into account by adding the information on household membership to generalised estimating equations (GEE) models [26,27]. Subgroup analyses will be used to evaluate whether the intervention effects differ between predefined subgroups of the population. Firstly, outcomes will be compared between older persons at high risk (Pra > 0.28) and those at low risk (Pra ≤ 0.28) for hospital use [10,11], based on the hypothesis that this type of intervention might have greater positive effects in persons at low risk [28]. Second, for the randomised study in Hamburg and Solothurn, an additional analysis will be carried out to evaluate the independent effects of the site-specific reinforcement on primary outcomes: multivariate regression analyses will be conducted using the composite scores as outcome variables, and participation status in the reinforcement as an independent variable, controlling for intervention allocation status and available participant base-line characteristics. Finally, sensitivity analyses will be conducted to evaluate for potential bias resulting from missing outcome data. First, all analyses will be repeated by adjusting GEE models for base-line age, gender, self-perceived health and number of physician visits reported. Second, primary outcome analyses will be repeated by using with composite scores of health behaviour and use of preventative care which will be derived from imputed outcome estimates in persons with partially missing information.

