We will also evaluate changes in preventative care use, health behaviour, and health status between baseline and the one-year follow-up among persons in the intervention group. This analysis will be possible because persons in the intervention group received the HRA-O questionnaire both at base-line and at one-year follow-up. This analysis will adjust for household membership and base-line variables (age, gender, self-perceived health status, health care use prior to base-line). These pre-post analyses will be restricted to the intervention group since primary outcomes were not measured in the control group at baseline.

Outcome analysis of data from the concurrent comparison group will include a comparison of primary and secondary outcomes between the intervention group and the concurrent comparison group. The primary analysis will be a comparison of primary outcomes adjusted for base-line factors.

Categorical and binary outcome data will be analysed using chi-square tests; continuous outcome data will be compared using t-tests if normally distributed, Mann-Whitney U test if skewed. Number of physician visits will be analysed with ordered logistic regression models. To allow for within-household clustering, Generalised Estimating Equations (GEE), assuming an exchangeable correlation structure, will be used to analyse all outcomes [27]. Data will be analysed using the SAS programme [29].

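### The planned reinforcement model (Hamburg, Solothurn) compares self-selected participants with non-participants inside the intervention arm, so it cannot estimate an independent effect of reinforcement

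*Protocol article*

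**What the plan says.** The Statistical analyses section of the protocol article announces, for Hamburg and Solothurn, that "an additional analysis will be carried out to evaluate the independent effects of the site-specific reinforcement on primary outcomes". The outcomes are the two composite scores. The model uses "participation status in the reinforcement as an independent variable, controlling for intervention allocation status and available participant base-line characteristics".

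The sections on the intervention show how participation arises:
- **Hamburg:** all intervention patients "were invited to participate in a 4-hour group session at a geriatric centre or to receive two home visits".
- **Solothurn:** "all participants who returned the HRA-O questionnaire were offered home visits by specially trained health nurses".
- **Both sites:** "Participants who completed the HRA-O questionnaire and their health care providers received the computer-generated personalised feed-back reports".
- **Controls:** "Those allocated to the control group received usual care".

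On covariates, the Data collection section says: "Information on base-line self-perceived health status, prior health care use, and instrumental support were derived from the Pra questionnaire". Age and gender came from practice registers. The Statistical analyses section also says that the primary outcomes were not measured in controls at baseline, whereas "persons in the intervention group received the HRA-O questionnaire both at base-line and at one-year follow-up".

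**The concern.** Putting allocation in the model looks as if it keeps the protection of randomisation. It does not. It moves the whole participation contrast inside one arm, where patients sorted themselves by accepting or declining an offer. People who accept a prevention session or nurse visits may well have had better health behaviour and more preventative care use beforehand, and those are the outcomes being scored. In Solothurn there are two sorting steps: returning the questionnaire, then accepting the visits.

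At stake is a statement that group sessions or home visits add something beyond the HRA-O. The allocation coefficient is also at risk of being read as the effect of HRA-O without reinforcement. The Discussion warns of selection bias for the concurrent comparison group but not for this analysis.

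**Working it through.** **1. What the coefficients mean.** Let A = 1 for intervention and P = 1 for participation in reinforcement. P = 0 for every control. Without covariates, the model score = b0 + b1·A + b2·P has three cells:
- controls: b0
- intervention non-participants: b0 + b1
- intervention participants: b0 + b1 + b2

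Hence b2 = mean(participants) − mean(non-participants), both within the intervention arm, and b1 = mean(non-participants) − mean(controls). A numerical check agreed to below 1e-12. With covariates, controls affect b2 only through the covariate slopes.

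**2. Effect on the allocation coefficient.** If a proportion π of the intervention arm participates, the randomised contrast equals b1 + π·b2. That contrast is protected by randomisation, so selection that raises b2 by δ lowers b1 by π·δ. Neither coefficient has a randomised interpretation alone.

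**3. What the covariates can remove.** The pre-randomisation data common to both arms are age, gender and the Pra items. Education, living alone and chronic conditions were collected from controls only at one year (text introducing Table 4). The baseline level of the outcome does not exist for controls, so it cannot be an ordinary covariate in a two-arm model.

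**4. Mixing with HRA-O receipt.** A non-returner had no feedback report at either site. In Solothurn a non-returner is also a non-participant by design. The documents give no return count for the intervention arm, but Table 4 gives an upper limit, because anyone who answered the living-alone item had returned the baseline HRA-O:
- Hamburg: 878 − 798 = 80; 80/878 = 9.1%
- Solothurn: 874 − 745 = 129; 129/874 = 14.8%

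These are maxima, since returners did skip items. The education item has 756 and 702 answers, so at least 798 − 756 = 42 and 745 − 702 = 43 people returned the form without answering it.

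**5. Illustration of size (assumed inputs).** The plan states no figure for this analysis to reproduce. The following was simulated with a true effect of zero:
- composite SD 20 points
- 80% of each arm evaluable (Hamburg 702 and 1362, Solothurn 699 and 1128)
- participation of 40%, 60% or 80%
- one measured baseline covariate, adjusted for
- an unmeasured motivation factor correlated 0.5 with the tendency to participate
- independent persons, no household clustering; 300 replicates per scenario

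| Motivation–outcome correlation | Mean participation coefficient (points) | Significant at 5% |
|---|---|---|
| 0 | about 0 | 4–6% |
| 0.1 | 1.6–1.8 | 15–23% |
| 0.2 | 3.3–3.6 | 52–62% |
| 0.3 | 4.7–5.3 | 83–94% |

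The randomised contrast stayed within about 0.13 points of zero throughout. The table shows the mechanism and its dependence on the assumptions; it does not estimate the bias in this trial.

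**The case against.** The strongest reply is that this is an additional analysis placed with the subgroup analyses, that it adjusts for baseline characteristics, and that the main intervention-versus-control comparison does not use it. The article also condenses an analytic plan that may list more covariates. All of this is fair, and it limits the weight of the point. It does not repair the model: the contrast stays within one arm whatever the covariate list, and no list can supply baseline outcomes that controls never gave.

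A reader might infer more than the documents support:
- **That a definite number of points of selection would be reported as effect.** Assuming a prior gap and carrying it through one-for-one only restates the assumption, and it ignores the planned adjustment.
- **That failure to return the HRA-O explains much of non-participation.** The 9.1% and 14.8% are upper limits on non-return, and without participation rates no share can be computed.
- **That the return condition held at both sites.** The article states it for Solothurn only. In Hamburg all intervention patients were invited, so a non-returner could still take part.
- **That a central aim of the study fails.** The Abstract and Discussion describe effects of HRA-O combined with differing reinforcement, which the site-specific randomised comparisons address.

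It is also true that restricting to returners leaves participation voluntary. The remedy reduces the confounding and does not abolish it.

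**Conclusion.** The point holds in limited form and should be acted on. As specified, the participation coefficient is a non-randomised, within-arm contrast that combines any reinforcement effect with residual self-selection and, through non-returners, with HRA-O receipt. No randomised arm at either site was assigned HRA-O without an offer of reinforcement, so the design itself cannot isolate an independent effect.

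The structural conclusion rests only on controls having no access to reinforcement and on allocation being in the model; the article states both. The direction and size of the bias are not known. Upward bias is plausible if engaged patients behaved better beforehand, but that is an assumption. The main randomised comparison at each site is untouched.

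**What to change.** Replace the two-arm model with one fitted among intervention patients who returned the baseline HRA-O. Regress the one-year composite on participation, adjusting for the person's own baseline composite and the pre-randomisation covariates, with household clustering handled by GEE as elsewhere in the plan. Receipt of the HRA-O feedback is then uniform, and prior behaviour is in the model.

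For Hamburg, report how many invited patients are left out because they did not return the questionnaire. At both sites, report the number who participated. Describe the result as a non-randomised association among HRA-O returners and drop the wording about independent effects. If the two-arm model is still shown, say that its allocation coefficient compares non-participants with controls and is not an effect of HRA-O alone.

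The cost is small: the baseline HRA-O data were already collected in this arm, so no new data collection is needed. The sample is smaller, the causal wording is given up, and selection among returners remains.

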### Sample size/power calculation

We calculated the required sample size for detecting, at a two-sided significance level of 0.05 and with a power of 80%, a postulated 30% difference in positive health risk behaviour or preventative care use in the intervention group as compared to controls at the one-year follow-up. For this calculation, a prevalence of positive behaviour or preventative care use among controls of 20% was assumed, based on pilot data in a comparable sample of community-dwelling older persons [6]. Based on a 1:1 randomisation ratio and a predicted drop-out rate at one year of 20%, the required sample size was 1000 persons per group. In Hamburg and Solothurn, due to limitations in resources available for offering the intervention (group sessions, home visits), a randomisation rate of 1:2 was preferable. Based on a 1:2 randomisation rate, and on the same drop out rate, the required sample size was 763 persons in the intervention group and 1525 persons in the control group.

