### Comparison between groups of participants

Table 4 describes the available base-line characteristics of the study participants according to study sites and group allocation. This is to evaluate the success of randomisation. Within each site, prevalence rates were similar between intervention and control groups. In contrast, there were some relatively minor, but statistically significant differences between persons of the concurrent comparison group and persons of the intervention group (Table 4). Information on education, living alone status, and chronic conditions was derived from baseline HRA-O questionnaire (intervention groups: administered at the start of the project after randomisation; control and concurrent comparison groups: administered at the one-year follow-up). Missing values are due to non-response (all groups) or attrition (death, move away, and move to nursing home) in the control and concurrent comparison groups.

**Table 4 T4:** Self-reported baseline characteristics of the PRO-AGE study participants, according to site and group assignment

**Baseline characteristics**	**London (U.K.)**			**Hamburg (Germany)**			**Solothurn (Switzerland)**		
	**Intervention group**	**Control group**	**Concurrent comparison group**	**Intervention group**	**Control group**	**Concurrent comparison group**	**Intervention group**	**Control group**	**Concurrent comparison group**

Age (years)	74.7 ± 6.4 (1240)	74.4 ± 6.2 (1263)	74.9 ± 6.5 (636)	71.9 ± 7.7 (878)	71.8 ± 7.6 (1702)	72.0 ± 8.2 (746)	74.5 ± 5.8 (874)	74.5 ± 6.1 (1410)	74.2 ± 6.0 (1171)
Female gender	55.3% (686/1240)	54.6% (689/1263)	57.5% (366/636)	61.5% (540/878)	63.3% (1077/1702)	68.2%* (509/746)	56.9% (497/874)	56.5% (796/1410)	57.0% (667/1171)
Fair/poor self-perceived health	24.5% (304/1240)	27.2% (343/1263)	27.4% (174/636)	38.6% (339/878)	38.5 (656/1702)	39.5% (295/746)	19.9% (174/874)	24.8% (349/1410)	23.6% (276/1171)
≥1 hospital admission over past 12 months	14.0% (173/1240)	14.6%) (185/1263)	14.2% (90/636)	21.2% (186/878)	21.2% (360/1702)	22.5% (168/746)	19.9% (174/874)	18.5% (261/1410)	17.7% (207/1171)
> 6 doctor visits over past 12 months	19.0% (236/1240)	24.3% (307/1263)	23.4% (149/636)	49.9% (438/878)	49.9% (849/1702)	44.0%* (328/746)	24.0% (210/874)	24.3% (343/1410)	28.7%* (336/1171)
No available caregiver if needed	17.6% (218/1240)	14.8% (187/1263)	19.2% (122/636)	17.8% (156/878)	18.9% (322/1702)	20.0% (149/746)	9.8% (86/874)	11.6% (163/1410)	8.8% (103/1171)

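### The GEE adjusted for baseline covariates, already planned at each site, should be the main randomised analysis, and the article should name the two modest arm differences in Table 4 that its text passes over

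*Protocol article*

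**What the plan says.** All references are to the Protocol article.

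- **Main analysis (Statistical analyses).** Intervention and control are compared at follow-up, separately by site, in GEE models that carry household membership. No baseline covariate is named for this comparison.
- **Adjusted analysis (same section).** "First, all analyses will be repeated by adjusting GEE models for base-line age, gender, self-perceived health and number of physician visits reported". It is the first of two sensitivity analyses, and the purpose given for both is bias from missing outcome data.
- **Tests named (same section).** "Categorical and binary outcome data will be analysed using chi-square tests", with t or Mann-Whitney tests for continuous outcomes. The same paragraph then says that GEE with an exchangeable correlation will be applied to every outcome.
- **Balance (Comparison between groups of participants).** "Within each site, prevalence rates were similar between intervention and control groups". The Discussion concludes that baseline findings confirm both the randomisation and the comparability of the arms.
- **Table 4 footnote.** Asterisks mark significant differences between the intervention group and the concurrent comparison group. No comparison of intervention with randomised control is marked.
- **Timing (Data collection).** Age and gender come from practice registers, and self-perceived health and prior health care use from the Pra questionnaire, all before randomisation.

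**The concern.** Two separate things are wrong.

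First, the model that uses the best available baseline information has been given a narrow role. Age, gender, self-perceived health and physician visits were picked by the authors as worth adjusting for. They precede randomisation, and in Table 4 the denominators for all four equal the full arm sizes. Several primary outcomes in Table 2 (blood pressure, cholesterol and glucose checks, influenza and pneumococcal vaccination) plausibly depend on how often a patient sees the GP. The article itself makes the adjusted comparison primary for the intervention versus concurrent comparison group. For the randomised comparison it treats adjustment only as a missing-data check, and it does not say which estimate governs if the two disagree.

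Second, evaluating the success of randomisation is one of this article's stated aims, and its summary is more favourable than its table. Two of the variables in the adjusted model differ between randomised arms by about 5 points, one in London and one in Solothurn. Because the asterisks test a different contrast, the reader gets no signal of this.

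At stake is a small conditional shift in some outcomes at two sites, and the risk that an unexplained gap between the unadjusted and adjusted results is settled after both have been seen.

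**Working it through.** **1. The design effect used as a yardstick.** The inputs are in Sample size/power calculation: "at a two-sided significance level of 0.05 and with a power of 80" per cent; "a postulated 30% difference in positive health risk behaviour or preventative care use in the intervention group as compared to controls"; "a prevalence of positive behaviour or preventative care use among controls of 20% was assumed"; "a predicted drop-out rate at one year of 20" per cent. Read as a relative difference, 30% of 20% is 6 points, so 20% vs 26%. The two-proportion formula with continuity correction gives 805 per arm, and 805 / 0.80 = 1007 (without correction, 772 / 0.80 = 965). The article says "the required sample size was 1000 persons per group". The corrected figure agrees within 1%, so 6 points is the effect the trial was sized for.

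**2. Arm differences from the Table 4 counts.** Pearson chi-square without correction. The standardised difference is (p1 − p2) / √{[p1(1 − p1) + p2(1 − p2)] / 2}.

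| Variable | Intervention | Control | Difference | Chi-square | p | Std. difference |
|---|---|---|---|---|---|---|
| London, >6 doctor visits | 236/1240 = 19.0% | 307/1263 = 24.3% | −5.3 points | 10.25 | 0.0014 | −0.13 |
| Solothurn, fair/poor health | 174/874 = 19.9% | 349/1410 = 24.8% | −4.8 points | 7.17 | 0.007 | −0.12 |

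These tests ignore households. Dividing each chi-square by an assumed design effect of 1.5 gives 6.83 (p = 0.009) and 4.78 (p = 0.029).

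**3. The rest of the table.** There are 15 binary pre-randomisation comparisons (five variables at three sites). The other 13 all have p > 0.05, the smallest being London, no available caregiver, 17.6% vs 14.8%, p = 0.06. Hamburg has p from 0.38 to 1.00 on all five. Mean age gives p = 0.23, 0.75 and 1.0 in London, Hamburg and Solothurn. A Bonferroni limit is 0.05 / 15 = 0.0033: London visits falls below it, Solothurn health does not.

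Hamburg low education also differs (18.8% vs 23.5%, p = 0.013), but it was collected after randomisation, for controls at one year, so it is not evidence on the allocation.

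**4. Possible size of the shift.** Conditional shift = arm difference × risk difference in the outcome between covariate levels. The article does not give the second factor, so 5 to 30 points is assumed.

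- London (5.27 points unrounded): 5.27 × 0.05 = 0.26 to 5.27 × 0.30 = 1.58 points. Divided by 6: 4% to 26%.
- Solothurn (4.84 points unrounded): 4.84 × 0.05 = 0.24 to 4.84 × 0.30 = 1.45 points. Divided by 6: 4% to 24%.

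**5. What that does to the test.** Assume a 20% outcome rate and 20% dropout, leaving 992 and 1010 in London. Then SE = √[0.16 × (1/992 + 1/1010)] = 1.79 points. In Solothurn, with about 699 and 1128, SE = 1.93 points. Given the observed imbalance, two-sided type I error is about 0.06 at both sites for a 10-point association. Over 5 to 30 points it runs from 0.052 to 0.14 in London and from 0.052 to 0.12 in Solothurn.

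**The case against.** The strongest reply is that nothing is invalid. The unadjusted comparison of randomised arms holds its error rate over repeated randomisation, and choosing a model because an imbalance was seen is a data-driven choice. That stands. It defeats the argument from Table 4 to a new primary model, but not the argument from covariates that were named in advance, measured before allocation and plausibly related to outcome.

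Next, two differences among 15 comparisons are not remarkable. If the comparisons were independent, two or more at p < 0.05 would occur with probability 1 − 0.95^15 − 15 × 0.05 × 0.95^14 = 0.17. Both are modest in standardised terms, and Hamburg shows none. This also stands, and a reader who infers that randomisation failed goes beyond the documents.

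Third, the adjusted GEE is planned for all analyses, so its estimate will exist. True; what is missing is its rank and a rule for disagreement.

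Two further inferences are tempting. One is that the chi-square, t and Mann-Whitney tests mean the main analysis ignores households. The same paragraph assigns GEE to all outcomes, so a clarifying clause is enough. The other is that the Solothurn count 174/874 is a misprint because the hospital-admission row prints it too. The percentage agrees with the count in both rows, so the repeat shows no error, although a look at the source data is cheap.

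**Conclusion.** The point holds in a limited form. The plan places a ready, pre-specified adjusted model below a household-only one and gives it a purpose that does not cover chance imbalance. The text on balance leaves out two differences that the table contains.

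The size is small to moderate: about 0.3 to 1.6 points in London and 0.2 to 1.5 points in Solothurn, or roughly 4% to 26% of the 6-point design effect, with nothing comparable in Hamburg. These figures rest on an assumed association of 5 to 30 points; the documents give no value. Direction is also assumed. If frequent attenders receive more preventative care, the London difference works against the intervention on those outcomes. In Solothurn the direction depends on how self-perceived health relates to each outcome.

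It would be wrong to conclude that the unadjusted result is biased in the usual sense, or that Table 4 by itself obliges a switch. The reason for adjusting is the advance choice of covariates.

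**What to change.** - **Statistical analyses.** Make the GEE adjusted for baseline age, gender, self-perceived health and number of physician visits the main analysis at each site. Give as the reason that the covariates were named in advance and are expected to relate to outcome. Report the household-only GEE beside it, and state that the adjusted estimate governs if they disagree.
- **Effect measure.** If a logit link is used (the article does not say), the adjusted odds ratio is a conditional effect and is not the same quantity as the unadjusted one. Report a marginal, standardised risk difference as well.
- **Test wording.** Add a clause saying that GEE governs inference for all outcomes.
- **Comparison between groups of participants, and the concluding paragraph of the Discussion.** Replace the general statement on balance with one that names the London doctor-visit and Solothurn self-perceived-health differences, calls them modest, and notes that Table 4's asterisks do not test intervention against control.

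The cost is low. The data are in hand and the adjusted model is already planned, so the extra work is the standardised risk difference and some rewording. Because baseline data have been seen, the change should be dated and made before outcomes are compared by arm.
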